### Exclusion Criteria:

1. Structural heart diseases.
2. Major congenital disorder or chromosomal disorder.

### Consent

Deferral of consent will be sort owing to the design of the study. Cerebral NIRS is increasingly adopted as standard of care across many North American NICUs and TNE is a universally accepted modality for assessment of hemodynamics which is presently being performed in our NICU. The proposed study is using these existing ancillary modalities of hemodynamic assessment in a timelier fashion. Under deferral of consent, written consent will be obtained within 7 days of delivery, after addressing questions from the parents.

### Study Procedure:

This will be a Non-Blind Randomized Control Trial.

The study will involve the following steps ([APPENDIX 1](#)):

- 1) The study population will be assigned by simple randomization to either Multimodal arm to receive multimodal hemodynamic assessment using the study guideline ([APPENDIX 5](#)) or Standard arm to be treated according to the standard approach operative in RAH NICU.

- 2) ELGANs recruited into Standard arm will have
  - a) Continuous cardiorespiratory monitoring using ECG leads or via an Arterial line, and pulse oximetry and intermittent non-invasive blood pressure monitoring as standard of care in the NICU. Continuous arterial blood pressure monitoring will also be obtained as appropriate when an arterial line has been placed under the clinical team's discretion.
  - b) TNE studies will be performed at the discretion of clinical team for concerns on cardiorespiratory status of the study population.
  - c) The current treatment protocol for hemodynamic compromise at our NICU is starting inotropic support if mean blood pressure (MBP) is less than the gestational age of the infant in the first 72 hours of life.
  - d) Cerebral NIRS monitoring for rScO2 using neonatal sensors is not routinely used in the NICU and its application for the standard arm will be up to clinical team discretion.
- 3) ELGANs recruited to the Multimodal arm will have the same monitoring outlined in 2a in a standardized manner.
  - a) Continuous cerebral NIRS monitoring for rScO2 using neonatal sensor will be attached to the forehead of the infant for first 72 hours of life ([APPENDIX 2](#)).
  - b) Hemodynamic assessment using TNE ([APPENDIX 3](#)) will be performed at 18-24 hours and 66-72 hours of life. Additional TNE studies will be performed at the discretion of the clinical team for concerns on cardiorespiratory status of the study population.
  - c) Zubrow's Normative BP chart will be used and MBP less than the third centile for the gestational age will be taken as low BP for the study.
  - d) Blood pressure values and NIRS data will be integrated along with the clinical/biochemical information every 6 hours as well as whenever there is a deviation from the normal range.
  - e) A comprehensive study guideline comprising of the clinical, biochemical and NIRS data will be used by the study team in such cases to derive to the hemodynamic assessment of the study subject.
  - f) The findings will be carefully integrated within the clinical context to reach a description of the hemodynamic status of the study infant ([APPENDIX 5 and 7](#)).
- 4) All neonates will have standardized assessment for lead related skin abrasions as per standard practice, neonatal pain and stress assessment (NPASS Score) as part of their standard care.
- 5) Developmental support care will be given by the support person during the TNE assessment as per standard unit practice.

- 6) The discontinuation of either or both NIRS and TNE will depend on the discretion of the clinical team. The reason for the discontinuation will be sorted. This does not constitute a deviation from the study protocol.
- 7) The admission, 24 hours, 48 hours, 72 hours and 7days mean and median VVR and VIS scores will be calculated in both Study and Standard arms. ([APPENDIX 4](#)).
- 8) Urine output will be monitored during the study period as a surrogate for renal function and urine output less than 1 ml/kg/hr will be considered as oliguria.
- 9) SNAPPE-II Scores, which is a validated disease severity score in preterm babies, will be calculated in both study and standard arm at admission, 72 hours and 7 days of life.
- 10) The study team will be available 24/7 for hemodynamic consultation and for the ease of making hemodynamic interpretation, each pathway in the comprehensive guidelines will be transcribed into individual flash cards that will be easily accessible to study team. ([APPENDIX 8](#)).

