## Outcome Measures

### Primary Outcome

The primary outcome would be VVR Score at 7days in both arms.

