## Data Management:

### Data Collection and Handling

Case report forms will be devised to aid data collection. The following patient demographics will be recorded: gestation, birth weight, type of pregnancy, type of delivery, antenatal morbidities (PIH, placental abruption, chorioamnionitis), antenatal steroids, antenatal MgSO4, Apgar Scores, and gender. Information will be collected about the active clinical issue and disease states at the time of the hemodynamic assessment. Data pertaining to cardiorespiratory support, ventilation requirement, inotropes requirement will be recorded during the first week of life. Data for the TNE cardiac function

studies will be collected in a separate datasheet and continuous NIRS data will be collected for the first 72 hours of life. Major morbidity data like BPD, NEC, ROP, severe brain injury, PDA and mortality will be collected for the purpose of validation of VVR Score in the transitional neonatal period. All data will be entered into REDCap Software and will be securely stored on an institutional computer that is password protected.

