### Analysis

All statistical analyses will be performed with the intercooled Stata Version 18.0 (College Station, Texas). All data will be anonymized for analysis and intention to treat analyses will be performed for primary outcome. All the tests will be two-sided (where applicable), and significance will be defined as p-value  $< 0.05$ . Univariate and bivariate analysis will be done to describe the sample. Categorical variables will be compared by Fisher's Exact Test and continuous variables by Student's t-test (two-sided). Logistic and linear regression models will be developed using forward and backward stepwise methods to examine the association between different VVR cut off (95th centile for the entire study cohort and literature derived cut off of  $VVR > 53^{25}$  that is associated with adverse outcomes in neonatal postoperative cardiac patients) and neonatal outcome. ROC curve will be used for the purpose of validation of the VVR Scores in neonates during the neonatal period.

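### The primary comparison is an unadjusted t-test after simple randomisation although gestation, birth weight and antenatal steroids are recorded: valid and powered as stated, but it forgoes precision at no saving

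*Protocol*

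**What the plan says.** Allocation is described in Study Procedure, item 1: "The study population will be assigned by simple randomization to either Multimodal arm to receive multimodal hemodynamic assessment using the study guideline" or the standard arm. The text names no stratification factor, block or minimisation.

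The Primary Outcome section reads "The primary outcome would be VVR Score at 7days in both arms". The Sample Size section treats this as a continuous outcome compared by a two-sample t-test: means 30 and 22.5, common SD 15, two-sided alpha 0.05, power 0.80, 64 per group, N = 128.

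The Analysis section states that "intention to treat analyses will be performed for primary outcome" and gives the tests: "Categorical variables will be compared by Fisher's Exact Test and continuous variables by Student's t-test (two-sided"). Regression appears only for another purpose: "Logistic and linear regression models will be developed using forward and backward stepwise methods to examine the association between different VVR cut off" and neonatal outcome. That is the validation of the score, not the comparison of the arms.

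Data Collection and Handling lists the baseline data: "The following patient demographics will be recorded: gestation, birth weight, type of pregnancy, type of delivery", and further on antenatal steroids.

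**The concern.** The Serious Adverse Event section describes the population as infants born from 23 weeks 0 days to 28 weeks 6 days. Neither the allocation nor the primary analysis takes account of where in that range an infant lies.

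The protocol itself gives reason to expect a link with the outcome. VVR is built from inotrope doses, ventilator settings and creatinine change (Appendix 4), and both arms' definitions of low blood pressure depend on gestation (Study Procedure, items 2c and 3c). The link to day 7 is indirect, since the standard-arm rule is stated for the first 72 hours, but it is plausible.

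Two things are at stake. Any variance that gestation, birth weight and steroids explain stays in the error term. And if one arm happens to receive more of the most immature infants, the estimate moves and no planned analysis adjusts for it. The trial is not blinded, so covariates added after an imbalance has been seen would be open to the charge of being chosen after the fact. The only model-building approach that the protocol describes is stepwise.

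**Working it through.** **Inputs from the protocol (Sample Size section).** Difference 7.5, SD 15, two-sided alpha 0.05, 64 per arm.

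**Assumed input.** R², the share of day-7 VVR variance explained by gestation, birth weight and antenatal steroids. The protocol gives no value, so a range is shown.

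**1. The plan's own figure.** Standardised difference = 7.5 / 15 = 0.5. The exact (noncentral t) calculation for 80% power gives 63.77 per arm, rounded up to 64. Power at 64 per arm is 80.1%. N = 128 is reproduced.

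**2. Power with adjustment at the same N.** Residual SD = 15 × √(1 − R²), entered in the same t-test calculation. The unadjusted N with equal precision is about 128 / (1 − R²).

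| Assumed R² | Residual SD | Power at 64 per arm | n per arm for 80% power | Equivalent unadjusted N |
|---|---|---|---|---|
| 0 | 15.00 | 80.1% | 64 | 128 |
| 0.05 | 14.62 | 82.1% | 61 | 135 |
| 0.10 | 14.23 | 84.1% | 58 | 142 |
| 0.20 | 13.42 | 88.1% | 52 | 160 |
| 0.30 | 12.55 | 91.8% | 45 | 183 |

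This is an approximation. Reducing the error degrees of freedom from 126 to 123 for three covariates lowers power by less than 0.02 percentage points. Chance correlation between arm and covariates costs a little more. With R² near zero there is nothing to gain.

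**3. Chance imbalance.** With 64 per arm, the difference between arms in a standardised covariate has SD √(2/64) = 0.177. The chance that a given continuous covariate differs by more than 0.25 SD is 2 × [1 − Φ(0.25 / 0.177)], about 16%.

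An imbalance of 0.25 SD in a prognostic index moves the unadjusted difference by √R² × 15 × 0.25:

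- R² = 0.10: 0.316 × 15 × 0.25 = 1.2 points, or 16% of the 7.5-point target.
- R² = 0.30: 0.548 × 15 × 0.25 = 2.1 points, or 27% of the target.

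For scale, the standard error of the unadjusted difference is 15 × √(2/64) = 2.65 points.

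**4. Unequal arm sizes.** Under Binomial(128, 0.5), a split of 57 to 71 or worse has probability 25%. Power at 57/71 is 79.7%. Averaged over all splits it is 79.8%, against 80.1% at 64/64.

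**The case against.** The strongest reply is that nothing here is an error. The t-test is a proper analysis of a simply randomised trial: type I error is held, the estimator is unbiased over repeated randomisations, and the shifts in step 3 are part of the variability that the 2.65-point standard error already covers. All of this stands. A reader might infer that the trial is underpowered or its primary test invalid; the documents support neither, because the stated power is met without adjustment.

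A reader might also infer that simple randomisation does harm by failing to deliver 64 per group. Uneven arms are likely, but the average cost is about 0.3 percentage points of power, so this is no reason for a change.

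The size of the gain is also open to challenge. It rests wholly on R², which the protocol does not give. Appendix 4 calls for caution: the inotrope part is zero without vasoactive drugs, the ventilation part is zero on CPAP, and creatinine change is floored at zero. A large linear R² cannot be presumed for such a score. That stands, and is why the range starts near zero and stops at 0.30.

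Lastly, covariate adjustment is often settled in a statistical analysis plan, and none is shown. The Analysis sentence on continuous variables is general and does not name the primary outcome. A missing covariate list alone would not be a point. But the Sample Size section ties the primary outcome to a t-test, and no other comparison of the arms is stated, so the protocol as written does choose an unadjusted analysis.

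**Conclusion.** The point holds as a matter of efficiency, not of validity. The protocol records prognostic baseline data and uses them neither in allocation nor in the primary comparison. For an assumed R² of 0.05 to 0.30, the unadjusted test forgoes about 2 to 12 percentage points of power at N = 128. It also leaves in the estimate a shift of about 1.2 to 2.1 VVR points (R² 0.10 to 0.30) if the prognostic index happens to differ by 0.25 SD between arms. Confidence is high on what the protocol specifies and moderate on the size of the gain, which would vanish if the covariates barely predict day-7 VVR. The change is worth making because the data are already collected, but the trial does not depend on it.

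**What to change.** In the Analysis section, state that the primary analysis is a linear regression of day-7 VVR on arm, gestation (in weeks, continuous), birth weight and antenatal steroids, by intention to treat. State that these covariates are fixed in advance and not selected stepwise, and that the unadjusted t-test is a sensitivity analysis. The sample size and data collection stay as they are.

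The wording is short, but timing matters. In a non-blinded trial the change must be made, dated and justified before anyone sees outcome data by arm. If data by arm have already been seen, keep the t-test as primary and report the adjusted model as a supporting analysis labelled as added later.

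If allocation is still open, randomising in permuted blocks of varying size stratified by gestation is an optional extra. The Trial Time Frame puts recruitment in 2019 to 2021, so this may no longer be possible. The adjusted model does not depend on it.

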## Rationale:

Using mean BP alone as the indication of treatment of neonatal cardiovascular compromise without taking into consideration the status of tissue perfusion may lead to unnecessary exposure of neonates to vasoactive medication. This medication can be potentially harmful to these extremely vulnerable patients. Analysis of a large neonatal database  has demonstrated that treatment of hypotension was associated with an increase in serious brain injury. This held true even after the blood pressure was included in the regression mode, suggesting that it is treatment of hypotension, rather than the presence of hypotension which is harmful. The common interventions, fluid boluses followed by inotropes, could as well be harmful. Observational data has shown an association of fluid boluses with intracranial bleeding and in animal models intraventricular hemorrhage after hypotension can be induced by rapid volume infusion. Fluctuations in blood pressure when inotropes are introduced are well known and could also trigger hemorrhage. Current standard approaches to evaluation and treatment of transitional circulatory problems in the preterm infant may be harmful. Therefore, it is essential that these approaches are adequately investigated.

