## Trial Objectives:

### Primary Objective

To determine whether a multimodal hemodynamic monitoring using combined TNE and cerebral NIRS can reduce inotrope use as evidenced by decreasing VVR Scores in ELGAN within the first one week of life.

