## APPENDIX 8: MUSE Trial Study Guideline-Flash Card

Low BP(MBP<3rd Centile) and Normal NIRS( 55 – 85%)

[figure not shown]

Low BP(MBP<3rd Centile) and Low NIRS( <55% )

[figure not shown]

Low BP(MBP<3rd Centile)and High NIRS( >85%)

[figure not shown]

Normal BP(MBP =3-90th Centile) and Low NIRS( <55%)

[figure not shown]

Normal BP(MBP =3-90th Centile) and High NIRS( >85%)

[figure not shown][figure not shown]

High BP(MBP >90th Centile) and Normal NIRS( 55 - 85%)

[figure not shown][figure not shown]

High BP(MBP >90th Centile) and Low NIRS( <55%)

[figure not shown][figure not shown]

High BP(MBP =3-90th Centile) and High NIRS( >85%)

[figure not shown][figure not shown]

Supplement: Supplement 1. — Trial Protocol [file jamanetwopen-e254101-s001.pdf]

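### The arms differ in the blood pressure criterion, review schedule and guideline as well as in NIRS and TNE, so the trial tests a whole strategy and cannot support the primary objective's attribution to TNE plus NIRS

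*Protocol*

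**What the plan says.** The Primary Objective is to determine "whether a multimodal hemodynamic monitoring using combined TNE and cerebral NIRS can reduce inotrope use as evidenced by decreasing VVR Scores" in the first week of life. It names two technologies and nothing else.

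Study Procedure item 1 describes the randomised contrast more broadly. Infants go either to the "Multimodal arm to receive multimodal hemodynamic assessment using the study guideline" or to the unit's standard approach.

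Item 2c gives the standard arm's rule for haemodynamic compromise: "starting inotropic support if mean blood pressure (MBP) is less than the gestational age of the infant in the first 72 hours of life". Item 3c, listed only under the multimodal arm, reads: "Zubrow's Normative BP chart will be used and MBP less than the third centile for the gestational age will be taken as low BP". Items 3d to 3f add integration of blood pressure, NIRS and clinical or biochemical data every 6 hours and at any deviation from normal, using a study guideline. Items 3a and 3b add continuous cerebral NIRS for 72 hours and TNE at 18-24 and 66-72 hours.

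The standard arm may also have either modality. TNE is done there at the clinical team's discretion, and for NIRS, "its application for the standard arm will be up to clinical team discretion".

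The flash cards in Appendix 8 are headed by an MBP centile band crossed with a NIRS band. The first, for example, pairs low BP "and Normal NIRS( 55 – 85"%.

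**The concern.** The Rationale objects to "Using mean BP alone as the indication of treatment of neonatal cardiovascular compromise" because this may expose infants to unnecessary vasoactive drugs. On that reasoning, the criterion by which blood pressure is judged can itself affect inotrope use. Changing it needs neither a NIRS monitor nor an echocardiogram. The multimodal arm has a different criterion, and inotrope dose enters the primary outcome directly through VIS.

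What is at stake is what the primary result may be said to show. If VVR is lower in the multimodal arm, the objective as worded invites the conclusion that TNE plus NIRS lowered it. The design has no arm with the changed blood pressure definition alone, and no definition common to both arms. It therefore cannot separate that conclusion from an effect of the blood pressure criterion, the six-hourly review or the guideline.

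**Working it through.** **1. What differs between the arms (Study Procedure, items 2 and 3)**

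| Component | Standard arm | Multimodal arm |
|---|---|---|
| Blood pressure criterion | MBP below gestational age starts inotropes, first 72 h | MBP below the third centile is low BP, an input to assessment |
| Review of BP and NIRS data | Unit practice | Every 6 h and at any deviation |
| Written study guideline | No | Yes |
| Cerebral NIRS | Discretionary | Continuous, 72 h |
| TNE | Discretionary | Two scheduled scans, plus discretionary |

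Five components differ. The Primary Objective names the last two. Those two are also not absent from the standard arm.

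**2. Where the blood pressure definition can act without NIRS or TNE**

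The visible Appendix 8 headings cover low BP with normal, low and high NIRS; normal BP with low and high NIRS; and high BP with normal, low and high NIRS. That is 3 + 2 + 3 = 8 of the 9 combinations. (The last high-BP heading prints the 3-90th centile range, which looks like a slip and does not matter here.) The combination without a card is normal BP with normal NIRS.

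Let G be gestational age in weeks, read as mmHg, and L the chart's third centile. L is not in the document.

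- If L < G, an MBP from L up to just below G meets the standard arm's start rule but is not low BP in the multimodal arm. With NIRS of 55-85% no card applies.
- If L > G, an MBP from G up to just below L does not meet the standard arm's rule but is low BP in the multimodal arm. With normal NIRS a low-BP card applies.
- If L = G, the two limits coincide.

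For a 26-week infant, G = 26, and the discordant band is |26 - L| mmHg wide, from 0 upwards. For an infant with normal NIRS, item 3c alone decides whether a low-BP card applies.

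**3. Link to the primary outcome**

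Appendix 4 gives VVR = VIS + VI + (ΔCr × 10), so inotrope dose is an additive term. The rule in item 2c covers 72 hours, while the primary VVR is at 7 days, or 7 × 24 = 168 hours. That leaves 168 - 72 = 96 hours between the end of the rule and the primary measurement, so the effect on the 7-day VIS may be indirect. The objective's claim about inotrope use within the first week is exposed more directly.

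**4. The plan's own figure, and what it is sized for**

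Inputs from the sample size section: means 30 and 22.5, difference 7.5, SD 15, two-sided α = 0.05, power 0.80. The standardised difference is 7.5 / 15 = 0.5. The noncentral t solution is 63.77 per group, which rounds up to 64 per group and 128 in total, with power 0.801. The stated 128 reproduces. It is sized for the whole difference between arms.

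Suppose, purely as an assumption, that a share f of the 7.5 points came from the blood pressure criterion and the rest from TNE plus NIRS. The remainder is 7.5 × (1 - f). The table shows what a comparison able to isolate that remainder would need, with SD 15 throughout.

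| f (assumed) | Remainder, points | Power at 64 per group | Total N for 80% power |
|---|---|---|---|
| 0 | 7.5 | 0.80 | 128 |
| 0.25 | 5.625 | 0.56 | 226 |
| 0.50 | 3.75 | 0.29 | 506 |
| 0.75 | 1.875 | 0.11 | 2012 |

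This is not evidence about f. The two-arm comparison cannot estimate f at any sample size. The table shows only that a claim about the components is a different claim from the one the trial is sized to test.

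**The case against.** The strongest reply is that the randomised contrast is already the whole package. Item 1 assigns infants to assessment using the study guideline, the hypothesis in the Background speaks of multimodal assessment, and the Rationale is to move away from mean blood pressure alone. Replacing the unit's blood pressure rule is then part of the strategy, and a strategy trial need not isolate its parts. This stands. It means the randomised comparison is not biased, and a reader who inferred that the primary analysis is confounded would go too far. The reply does not rescue the objective's wording, which is narrower than item 1.

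Second, items 2c and 3c are different kinds of statement. Item 2c starts treatment, while 3c defines a category that feeds an assessment. The pathway figures in Appendices 5 and 8 are not shown, so the treatment consequence in the multimodal arm cannot be read. A reader might infer that infants between the two limits receive inotropes in one arm only; the visible text does not support that.

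Third, every card crosses blood pressure with NIRS, and normal BP with abnormal NIRS has its own cards. An infant not called low is therefore not removed from assessment. This stands too. The narrower observation, about infants with normal NIRS, is unaffected.

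**Conclusion.** There is a real mismatch between the stated objective and the contrast that is randomised. The trial can support a conclusion about the guideline-based strategy as a whole against unit practice. It cannot support attribution of an effect to TNE plus NIRS.

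The size and direction of the blood pressure criterion's contribution are unknown. They depend on chart values, pathway content and the share of VIS in the 7-day VVR, none of which the document gives. A reader might infer that most or all of the planned 7.5 points could come from the threshold, or that a null result would hide a monitoring effect. The documents support neither: the discordant band could be zero, and its direction is not known.

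The conclusion assumes that item 3c applies to the multimodal arm only. Its reference to the study is slightly ambiguous, but it sits under that arm and item 2c gives the standard arm its own rule. The matter concerns the wording of the objective and conclusion; the sample size and primary analysis are unaffected.

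**What to change.** Reword the Primary Objective in line with Study Procedure item 1. For example: to determine whether a guideline-based multimodal haemodynamic strategy (study blood pressure definition, six-hourly integrated review, continuous cerebral NIRS, scheduled TNE and written guideline), compared with the unit's standard approach, lowers VVR in ELGAN. Limit the permitted conclusion in the same terms, and state that the effects of the components are not separable in this design.

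Optionally, and as description only, classify recorded MBP in the first 72 hours against both limits in both arms, and report inotrope starts by class and arm. This must not be presented as isolating the NIRS or TNE effect. Starts that were avoided are not observed, and fewer starts between the limits could reflect the definition, reassuring NIRS, TNE or the review. The data collection section lists inotrope requirements but not MBP at each start, so availability needs to be confirmed first.

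The rewording needs no new data and no change to sample size, analysis or either arm's treatment rule. Its cost is a narrower claim. It takes no position on which blood pressure criterion is right.
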